### Outcomes Measurement

Outcomes include the complete spontaneous bowel movements (CSBMs), spontaneous bowel movements (SBMs), stool consistency (Bristol Stool Scale), straining during the defecation, rescue medicine or other measures used, and the questionnaire of Patient Assessment of Constipation Quality Of Life (PAC-QOL). Patients will record their bowel movements, constipation-related symptoms, medicine used for constipation, and daily diet 24 hours per day for 22 weeks.

The SBMs are the bowel movements that occur in the absence of rescue medicine, or other assistant methods (laxatives, enemas, suppositories usage, or digging out by fingers) within the preceding 24 hours, which include the CSBMs. When participants used rescue medicine, or other measures for constipation, the defecation within 24 hours was considered a non-spontaneous bowel movement, whereas defecation exceeding 24 hours was deemed a SBM. CSBMs were the SBMs with the sensation of complete evacuation. Outcome record time point: Baseline (week 0), week 2, week 4, week 6, week 8, week 12, week 16, and week 20.

Outcome assessing time point: week 4, week 8, and week 20.

Outcomes assessing is based on the patients' defecation diaries from the first week of screening period (week -2) until the last week of the follow-up period (week 20).

#### **2.4.7.3 Defecation Diaries:**

##### Defecation diaries during the treatment period (week 1–week 8):

Participants will record their bowel movements (BMs), SBMs, complete defecating or incomplete defecating, stool consistency, degree of straining, the time, dosage, and frequency of rescue medicine or other assistant methods used, and the abnormal diet or not on the diaries every day from the baseline to the end of week 8. Distribution of the defecation diaries: the diary of week 1 will be distributed at the first treatment of week 1, and the diary of week 2 will be distributed at the last treatment of week 1; the diary of week 1 will be taken back at the first treatment of week 2, and the diary of week 3 will be distributed at the last treatment of week 2; and so on. The diary of weeks 9–12 (follow-up period) will be distributed at the last treatment of week 8. Participants should return the diary of week 8 within week 9.

##### Defecation diaries during the follow-up period (week 9–week 20):

Participants will record their bowel movements (BMs), SBMs, complete defecating or incomplete defecating, and the time, dosage, frequency of rescue medicine or other assistant methods used on the diaries every day from the first of week 9 to the end of week 20. Distribution of the defecation diaries: research assistants should distribute 4-week diaries at once. The diaries of weeks 9–12 will be distributed at the last treatment of week 8. Within week 9, participants should return the diary of week 8, and get the diaries of weeks 13–16; within week 13, participants should return the diaries of weeks 9–12, and get the diaries of weeks 17–20; within week 17, participants should return the diaries of weeks 13–16; within one week after week 20, participants should return the diaries of weeks 17–20.

For the participants who do not abide by our treatment protocol strictly, the outcome evaluators should still follow them up through phone, text or a visit to record the related items.

#### **2.4.7.4 The success of participants blinding**

We will evaluate the rate of the successful blinding between EA and SA in 140 subjects (70 from EA group, and 70 from SA group; 9 to 10 participants at each site), who will be selected at random from our participants. After five minutes of the subjects' last treatment of week 4 and week 8, they will be asked if they have received the EA treatment. We will compare the proportions of the patients choosing EA treatment between the two groups.

### **3. Safety Assessment**

#### **3.1 Adverse Events**

The adverse events are some unintended symptoms, physical signs, or health conditions that show up after starting the interventions. A health condition or an illness existing before the treatment can be reported as an adverse event (AE) if the situation becomes worse after the treatment. An abnormal result of the laboratory examination can be reported as an AE only if it causes some clinical symptoms, and requires related therapies. We will observe the adverse events by asking the participants' non-inducing questions at each assessing point. We will also observe the adverse events through participants' self-report, or through physical examination, or by laboratory examination. All the adverse events must be recorded on the CRF. If an AE was observed, the following information should be provided:

1. Degree of severity (mild, moderate, severe);
2. If it is related to the interventions (affirmably, very likely, possibly, possibly not, affirmably not);
3. Duration of the AE (start and end dates, whether still exists at the end of the trial);
4. Severe adverse effect (SAE) or not.

SAE is defined as any of the following:

1. Fatal or life threatening;
2. Permanent or conspicuous loss of function or disability;
3. Congenital deformity or birth defect;
4. Need hospitalization or need prolonged hospitalization;

5. Severe medical accidents, which require medical or surgical interventions to prevent any of the above occurs.

Solution for controlling the adverse events:

- Further observing, without any treatment;
- Adjusting or stopping the treatment;
- Aborting the trial permanently;
- Adding combined drugs therapy;
- Giving non-pharmacologic therapy;
- Hospitalizing or prolonging hospitalization.

All the treatment measures for the adverse events should be recorded in detail on the CRF. We will follow up the adverse event through the whole trial until it is solved. We will confirm that if it is permanent. At every assessing point, we will evaluate the adverse event's severity, relation to our interventions, and the treatment measures. The common adverse events related to the interventions are listed in the investigator's brochure. During the updating of the brochure, related adverse events will be announced by the form of investigator's note (IN). We will also discuss with the participants about the adverse events that might occur during the trial.

### **3.2 Report of the Severe Adverse Event (SAE)**

For participants' safety, from the day they sign the informed consent until within 30 days after the end of the study, any SAE no matter if it is related to our interventions should be reported to [name] (Project management office, Acupuncture Department, Guang'anmen Hospital of China Academy of Chinese Medical Sciences; [name]) within 24 hours. SAE occurs over 30 days after the end of the study will not require reporting, unless it is related to our interventions. The reoccurrence, complication, or the progression of a reported SAE will be reported as the follow-up information of that SAE within 24 hours. All the information of the SAE will be collected and recorded on the form of SAE. Researchers should assess the relation of the SAE with our interventions, and fax the finished SAE form to the department of Integrated Medical Safety (IMS) of our project at Guang'anmen Hospital within 24 hours. The SAE form and the fax will be kept together with the CRF in the research center.

#### Safety Evaluation:

1. Safe, no adverse event, no abnormal examination of the safety index;
2. Relatively safe, mild adverse event with no treatment needed, no abnormal examination of the safety index;
3. Having safety problems, moderate adverse event which needs relative treatment, mildly abnormal examination of the safety index;
4. Withdrawal from the study due to the severe adverse event, or obviously abnormal examination of the safety index.

### **3.3 Safety related to EA**

Adverse events will be recorded and measured both by participants themselves and acupuncturists. Acupuncturists are responsible for the recording of the EA-related adverse events on the CRF. The adverse events relating to acupuncture include broken needle, needle left in the body after treatment, nausea during acupuncture, fainting caused by needling during the treatment, pricking lasted more than half an hour (no matter how much the intensity is) after acupuncture, hematoma or bleeding around the site of needling, numbness or infection around the site of needling, sleeplessness after acupuncture, dizziness after acupuncture, other discomforts (including palpitation, headache, anisotopia, drowsiness, or aggravation of existing symptoms) after acupuncture. Acupuncturists will record the symptoms, frequency, degree, and the duration of each AE. The pricking caused by needling will be assessed through 10-point visual analog scale (VAS). We will compare the proportion of participants who get acupuncture-related adverse effects, and the frequency of occurrence of each adverse effect between EA and SA groups. Participants who get acupuncture-related adverse effects at least once will be counted in for the comparison of the proportion.

### **4. Interventions**

Needle instrument: Huatuo disposable needles (size 0.30mm×25mm, 0.30 mm×40mm, 0.30 mm×50mm, 0.35mm×75mm, Suzhou Medical Appliance, Suzhou, Jiangsu Province, China),

Electro-acupuncture apparatus: Huatuo electro-acupuncture apparatus (type SDZ-V, Suzhou Medical Appliance, Suzhou, Jiangsu Province, China) will be used.

#### **4.1 Electro-acupuncture (EA)**

Acupoints:

Bilateral Tianshu (ST 25), Fujie (SP 14), Shangjuxu (ST 37).

Location:

According to the WHO Standardized Acupuncture Points Location.

Manipulation:

After sterilizing the skin in participants with supine position, needles of the size of 0.30 mm×50 mm, or 0.35 mm×75 mm will be inserted into ST25 and SP14 slowly and vertically, without manipulation, for approximately 30 to 70 mm until they pierced the muscle layer of the abdominal wall. Paired alligator clips of the EA apparatus will be attached transversely to the needle holders of the bilateral ST25 and SP14. EA stimulation will last for 30 minutes with a dilatational wave of 10/50Hz and current intensity of 0.1 to 1 mA. The skin around the acupoints shivering mildly indicates the proper dose. Needles of the size of 0.30 mm×40 mm will be inserted into ST37 vertically for about 25 to 30 mm. Three small equal manipulations of twirling, lifting and thrusting will be performed. The participants' feeling of sore and distention show the proper manipulation. The manipulation on ST37 mentioned above should be performed every 10 minutes, three times in 30 minutes.

Course of treatment:

Each participant will accept an 8-continuous-week treatment with 28 sessions in total. The participants will be treated 30 minutes once, once a day, five times per week in the first two weeks, and three times per week in the latter 6 weeks.

#### **4.2 Sham electro-acupuncture (SA)**

Acupoints:

Bilateral sham-Tianshu (sham-ST25), sham-Fujie (sham-SP14), and sham-Shangjuxu (sham-ST37)

Location:

Sham-ST25 locates laterally and horizontally from ST25, in the middle of the spleen and stomach channels. Sham-SP14 lies laterally and horizontally from ST14, in the middle of the spleen and stomach channels. Sham-ST37 stands laterally and horizontally from ST37, in the middle of the stomach and gallbladder channels.

Manipulation:

After skin disinfection in participants with supine position, needles of the size of 0.30 mm×25 mm will penetrate the skin uprightly at approximately 3–5 mm without any manipulation. Paired alligator clips of the specially made EA apparatus (power output lines, which connect the alligator clips and the EA apparatus, will be cut inside with an appearance as usual) will be attached transversely to the needle holders of the bilateral sham-ST25 and sham-SP14. The EA apparatus will be turned on with a working power indicator and the same sound as the EA group. These will suggest the participants that the EA apparatus is working, however there is no current output. Needles of the size of 0.30 mm×25 mm will penetrate into bilateral sham-ST37 vertically at about 3–5 mm without any manipulation.

Course of Treatment:

The course is the same as EA.

All the participants will be treated separately in order to prevent their communication with each other. Our 22-week trial contains 2 weeks of screening period, 8 weeks of treatment period, and 12 weeks of follow-up period (Figure 2). Collecting points of the outcomes: week -2 (screening), week 0 (baseline), week 2 (treatment), week 4 (treatment), week 6 (treatment), week 8 (treatment), week 12 (follow-up), week 16 (follow-up), week 20 (follow-up).

[figure not shown]

**Figure 2 The study period and assessing timeframe of our trial**

### 4.3 Rescue Medicine

If the participants don't have a bowel movement for 3 or more consecutive days during the whole trial period, they are allowed to use glycerol enema 110ml, or sorbitol enema 40–60ml once into anus as a rescue medicine. The time, frequency, and dosage of the rescue medicine used should be recorded at length on participants' defecating diaries. Other drugs for constipation are not allowed in our trial. However, if the participants have used any other drug, they must faithfully record on their diaries the name, time, frequency, and dosage of the drug used.

### 5. Informed consent

## 6. Quality Control

### 6.1 Quality Control

In our trial we will try to avoid selection bias as far as possible by using central randomized controlled design, and also by strictly including the participants according to the clear inclusion and exclusion criteria. Participants and the professional evaluators will be blinded; the statisticians who take care of our statistical analysis will also know nothing about patient assignment.

We have 3 levels of quality control:

Level 1: one or more researchers from each site will be assigned to check the performance of the trial.

Level 2: three or more researcher staff from Guang'anmen Hospital will be assigned to inspect the performance of the trial at all sites.

Level 3: five or more researchers from the Institute of Basic Research in Clinical Medicine, China Academy of Chinese Medical Sciences will be assigned to audit the performance of the trial at all sites.

We will perform the inspection and auditing in December 2012, in the middle of 2013, and in the middle of 2014.

### 6.2 Quality Guarantee

Before the start of the clinical trial, we will have a clinical training for all the researchers. After the training, the researchers should be familiar with the trial protocol, and the standard operation procedure (SOP) of the trial's performance.

### 6.3 Compliance Improvement

$$\text{Rate of compliance} = \frac{\text{The times of the treatment accepted by the participant actually}}{\text{The times of the treatment according to the protocol}} \times 100\%$$

The rate of compliance no less than 80% will be considered as a good compliance. To improve the participants' compliance, we will take measures as followed:

- Participants should participate the trial of their own accord, and sign the informed consent;
- Researchers should communicate with the participants frequently, patiently, and with concern for getting a better physician-patient relationship, and explain the related examination, interventions, and form filling at length.
- Researchers should record the participants' contact information in detail for the convenience of the follow-up.
- Before the randomization, researchers should inform the participants that all the cost referring to the examination and treatment would be exempted. Participants who complete all 8-week treatment and 12-week follow-up will get a subsidy of 180 RMB.
- The defecation diaries of the screening and treatment periods will be distributed weekly. The diaries of the follow-up period will be distributed every 4 weeks. Assessor should take back the completed diaries in time, and verify the related items with the participants.
- We will afford rescue medicines for the participants for severe constipation.
- We will remind the participants to fill in their defecation diaries in time by affording them brochures, or by texting.
- For participants who have less compliance, we will still follow them up for recording the related outcomes through phone or message.

### 6.4 Data and Safety Monitoring Board (DSMB)

To monitor the data and safety of this study, a DSMB composed by 7 experts will be organized before the starting of the trial. The overall responsibility of the DSMB is to protect the ethical and safety interests of subjects recruited into the project "The Efficacy and Safety Study of Electro-acupuncture for Severe Chronic Functional Constipation - a Multicenter, Randomized Controlled Trial", while protecting as far as possible the scientific validity of the data. The DSMB will have meeting at predefined times as at least twice a year to evaluate primary endpoint, to identify potential treatment harm and all cause mortality/morbidity and to identify potential treatment benefit. The data and safety-monitoring plan of DSMB is in detail in the Appendix.

## 7. Data Management

### 7.1 Flow Chart of the Data Management

[figure not shown]

**Figure 3 Flow chart of the data management**

## **7.2 The Raw Data Management and Archiving**

We use Remote Data Capture (RDC) system to perform data entry. The research assistants will fill out all the electrical CRF through RDC system. Researchers will inspect the eCRF, and signed electrically for the eCRF going into effect. The eCRF and the trace of eCRF revising will be left in the Oracle database.

## **7.3 Data Entry and Storage**

### **7.3.1 Database Building and Testing, Data Entry Interface**

The eCRF will be noted through CDISC SDTM standard, and the data entry interface will be generated through the Oracle Clinical software. The data entry interface should be in accordance with the paper-version CRF as far as possible. The inputted data will be stored in the Oracle database.

After preliminarily setting up the database, the entry clerks will input some analog data according to the CRF to test the database. The testing contains: (1) the agreement of the data entry interface and the paper-version CRF; (2) the agreement of the exported data from the database and the analog data; (3) the agreement of the structure of the exported database and the paper-version CRF. After the testing, data administrators should revise the database and make a testing report. Then they electrically signed on the approval page of the database to indicate that the testing is completed. The electrical files of the analog CRF, Noted CRF, screenshot of the data entry interface, database testing report, and the approval page of the database should be saved. If the database updates during the trial, the electrical files mentioned above are also need to be updated.

### **7.3.2 Data Entry and Inspection**

The research assistants take charge of the data entry for our trial. Before the entry, all the research assistants will accept the related training according to the data entry handbook. Researchers will inspect the database, and then sign electrically to let the data go in to effect.

## **7.4 Data Verification and Problems Solving**

Researchers will verify the data through Data Verification Plan (DVP) approved by the data administrator and the statisticians. Data queries will be inputted to a data query database, and form the DCF. After being inspected, the DCF will then be handed back to the original site, and the researchers of the site should answer the queries. Any revision of the database will be recorded through the RDC software.

## **7.5 Medical Coding**

A data administrator who has the medicine background will take charge of the medical coding. The contents of the coding are the clinical history, adverse events, and combined medication. The clinical history and adverse events will be coded through MedDRA dictionary (Version 13.0), and the combined

medication will be coded via WHO DD dictionary (Version 2007.03). The lead researchers will verify the coded e-files.

#### **7.6 Data Report**

Data report contains the aspects as followed: (1) members of the project; (2) disagreement from the primary data management plan; (3) actual finish time of every project; (4) problems and the solution during the data management (if have any); (5) reconstruction of the database (if have any); (6) distribution of the participants; (7) participants who disobey the trial protocol; (7) classifying plan of the statistical analysis population.

Data report will be performed monthly since the first entry of the eCRF.

#### **7.7 Data Auditing and Blinding Review**

When the data checking is finished, a data auditing and blinding review meeting will be hold. On the meeting, the data administrators, statisticians, researchers, clinical inspectors, and other related members would have a discussion on the following items according to the data management report and the data lists:

- Distribution of the participants;
- Protocol disobeying or not;
- Possible outlier;
- Baseline data;
- Outcomes;
- Statistical analysis plan.

Participants will be classified to their suitable statistical analysis sets according to the definition in the protocol. No patient can be excluded from the analysis, unless getting the permission of the meeting participants. All the meeting participants should sign the data locking consent, and the data auditing resolution.

#### **7.8 Database Locking**

The database will be locked if it fulfills all the aspects as followed:

- All the queries have been solved, and the database has been updated;
- No query has been found through the data inspection;
- The medical coding has been completed;
- The plan of the participants ' classification has been approved;
- The final draft of the SAP has been made, and approved by the project leader.

The leader of the DSMB (Table 1), statisticians and the data administrators will signed the data locking form, and then the database will be locked. The locked database will be sent to the statisticians for further statistical analysis through the data format of SAS.

### **8. Data Analysis**

#### **8.1 Objectives and Hypothesis**

The main objective is to compare the change of mean weekly CSBMs over the 8-week from baseline in the two groups. And we hypothesize that EA is better than SA in increasing CSBMs, relieving the related symptoms of severe constipation, and improving the quality of life.

#### **8.2 Statistical Analysis Population**

Randomization population will be adopted. According to the intention-to-treat principle, the participants who accept randomization will be included in the randomization population regardless of whether they receive any treatment. Missing data will be handled with multiple imputation methods. The Institute of Basic Research in Clinical Medicine, China Academy of Chinese Medical Sciences and the Biostatistics center in the University of Washington (Seattle) will be responsible for the statistical analysis.

#### **8.3 Statistical Contents and Methods**

All statistical analyses will be two-sided tests. For all statistical analyses, SAS 9.4 software will be used. A P value of less than 0.05 ( $\alpha$ -value of 0.05) is considered to indicate statistical significance.

Analysis of baseline characteristics will analyze the demographic data and other baseline measures. Mean and standard deviation will be used in the continuous variables and percentages in the categorical variables. For comparisons the two independent sample, t-test will be used for continuous variables and Chi-squared test for categorical variables. Non-parametric tests may also be used. A Fisher Exact test will be used to describe the case distribution in the EA group and the SA group and to calculate the total dropout rate and the dropout rate caused by adverse events between the two groups. A Chi-square test is used to analyze the difference in compliance between the two groups to evaluate if the participants in the EA group and the SA group receive the specified treatment according to the protocol.

As the main objective is to compare the changed number of weekly average CSBMs throughout the 8 weeks of treatment with the average weekly CSBMs during the 2 weeks baseline period, the primary analysis of the patient-level data is the number of CSBMs per week for 8 weeks. It means the total amount of CSBMs during 8 weeks will be divided by eight to achieve the result. (Each patient therefore has one number of weekly CSBMs throughout the 8 weeks of treatment). The null hypothesis is this number of CSBMs is the same between the EA and SA groups, and the alternative hypothesis is that the change from baseline in CSBMs at 8 weeks for the EA group does not equal the SA group. The subjects who do not receive any treatment after randomization or receive treatment but not any efficacy assessment data are classed as missing data, and multiple imputation methods will be used to deal with the missing data. An analysis of covariance (ANCOVA) will be used group, study site and baseline CSBMs will be included in the ANCOVA model. The secondary outcome measures include the following seven items: 1) the proportion of participants with three or more mean weekly CSBMs during weeks 1–8 and weeks 9–20; 2) the change from baseline in mean weekly CSBMs during weeks 9–20; 3) the change from baseline in mean weekly spontaneous bowel movements (SBMs); 4) the change from baseline in mean stool consistency over weeks 1–8; 5) the change from baseline in mean straining scores over weeks 1–8; 6) the change from baseline in PAC-QOL scores at week 8; 7) the proportion and mean weekly frequency of rescue medicine and other defecation assistances used. Chi-square test was used to compare the proportion of participants having three or more CSBMs and the proportion of other rescue medicine and other defecation assistances used between two groups. Student's t test was used to compare the change from baseline of mean weekly SBMs and the scores in PAC-QOL, stool consistency, and straining between groups. Wilcoxon rank sum test was used to compare the mean weekly frequency of other rescue medicine and other defecation assistances used between groups. Subgroup analysis will be conducted according to the subject's age (<65 years and ≥65 years). All adverse events and serious adverse events will be listed. Poisson regression model will be used to compare the incidence of adverse events between the EA and SA groups.

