**Figure 1 Flow Chart**

#### 2.4.4 Sample Size

According to our pilot study, the weekly CSBMs increase was conservatively estimated at 1.49 times, with a standard deviation of 1.77, after 8 weeks EA treatment; the weekly CSBMs increased by 1.01, with a standard deviation of 1.61, after 8 weeks SA treatment. We used SAS 9.3 to define the 95% power, using a one-way analysis of variance fixed effects omnibus test, assuming a 20% loss to follow-up. To ensure the stratified randomization, the sample size calculation result is 1034.

1034 participants were enough to provide 95% power to detect a difference of 0.5 in the change of weekly CSBMs between the two groups at a significance level of 5% using analysis of variance. The intergroup difference of 0.5 weekly CSBMs was within the range of published estimates of the minimum clinically important difference (MCID) for weekly CSBMs.

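### Section 8.3 classes never-treated randomised participants as missing by treatment status rather than by absence of outcome data, which does not fit the intention-to-treat principle in section 8.2

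*Protocol*

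**What the plan says.** Section 8.2 adopts the randomised population under the intention-to-treat principle: "the participants who accept randomization will be included in the randomization population regardless of whether they receive any treatment". It adds that missing data will be multiply imputed.

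Section 8.3, describing the primary analysis, says who counts as missing: "The subjects who do not receive any treatment after randomization or receive treatment but not any efficacy assessment data are classed as missing data". It continues that "multiple imputation methods will be used to deal with the missing data". The imputation model is not described.

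Three other places bear on whether untreated participants can have outcome data:

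- Section 2.4.7.3, at the end of the text on follow-up diaries, says of participants who do not keep strictly to the treatment protocol that "the outcome evaluators should still follow them up through phone, text or a visit to record the related items".
- Section 6.3 says: "For participants who have less compliance, we will still follow them up for recording the related outcomes through phone or message".
- Section 2.4.7.3, on treatment-period diaries, says that "the diary of week 1 will be distributed at the first treatment of week 1".

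**The concern.** The sentence in 8.3 has two limbs, built differently. A treated participant is missing only if no efficacy data exist. An untreated participant is missing outright, with nothing said about data. For that second group the rule turns on what happened to treatment, not on what was observed.

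An intention-to-treat analysis needs everyone randomised to be counted, and it needs the outcomes they actually had to be used when available. Section 8.2 secures the first. Section 8.3, followed literally, gives up the second for never-treated participants, while 2.4.7.3 and 6.3 ask staff to keep collecting outcomes when treatment is not followed. If those outcomes are replaced by values drawn from treated participants, the primary estimate moves towards the effect had everyone started treatment, while still being labelled intention-to-treat.

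This is more than detail that could wait for the SAP. An SAP that followed the sentence would set aside observed outcomes, and one that did not would depart from the protocol.

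**Working it through.** **Reading the passages together**

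| Participant | Status under 8.3 | Condition on data? |
|---|---|---|
| Treated, some efficacy data | not classed as missing | yes |
| Treated, no efficacy data | missing, imputed | yes |
| Never treated, no outcome data | missing, imputed | none stated |
| Never treated, outcomes obtained | missing, imputed | none stated |

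Only the last row conflicts with 8.2. In the third row imputation is what 8.2 already provides.

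**Size and direction**

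The protocol states no figure for this effect, so there is nothing to reproduce. The inputs are:

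- From section 2.4.4: mean change 1.49 (SD 1.77) for EA and 1.01 (SD 1.61) for SA, a difference of 0.48. The check takes these as the means of treated participants. The total sample is 1034 and the target difference is 0.5.
- Assumed, because the protocol gives no values: the never-treated shares pE and pS, and the mean change u among the untreated, taken as equal in both arms.

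*Imputation within arm.* The untreated receive the mean of their own arm's treated participants, so the analysis returns 1.49 − 1.01 = 0.48. With the untreated participants' own outcomes the difference is

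[(1 − pE) × 1.49 + pE × u] − [(1 − pS) × 1.01 + pS × u].

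Subtracting this from 0.48 gives

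bias = pE × (1.49 − u) − pS × (1.01 − u).

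| Case | Formula | 1% | 3% | 5% |
|---|---|---|---|---|
| Equal shares f, any u | +0.48 × f | +0.005 | +0.014 | +0.024 |
| EA only, u = 0 | +1.49 × f | +0.015 | +0.045 | +0.075 |
| SA only, u = 0 | −1.01 × f | −0.010 | −0.030 | −0.051 |

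For u below 1.01, the sign turns negative once pS/pE exceeds (1.49 − u)/(1.01 − u). That is 1.49/1.01 = 1.48 at u = 0, and 0.99/0.51 = 1.94 at u = 0.5. For example, with pE = 2%, pS = 5% and u = 0, the bias is 0.02 × 1.49 − 0.05 × 1.01 = 0.0298 − 0.0505 = −0.021.

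*Imputation model without group.* The untreated in both arms receive about the same value. At equal shares the estimate is then 0.48 × (1 − f), which equals the difference based on their own outcomes, so there is no bias towards EA.

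**Scale**

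With 517 per arm the standard error of the difference is about √[(1.77² + 1.61²)/517] = √(5.725/517) = 0.105. The equal-share bias at 5% is 0.024/0.105 = 0.23 of one standard error, and 0.024/0.5 = 4.8% of the target difference.

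All these figures suppose that every never-treated participant has outcomes that are set aside. Where none exist, the 8.3 rule discards nothing.

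**The case against.** The strongest reply is that the sentence was only meant to say who lacks a primary outcome. The week 1 diary is given out at the first treatment session, so someone who never attends gets no routine treatment-period diary. For most such people, never treated and no 8-week data are the same thing. The follow-up provisions in 2.4.7.3 and 6.3 concern imperfect adherence in general; neither names the never-treated, and the first sits in the text on weeks 9–20. This stands as a limit on the practical effect. It does not rescue the wording: untreated participants are not carved out of those provisions, so outcomes can exist, and the rule has no place for them.

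It is also fair to say that nobody is excluded. A reader might infer that untreated participants drop out of the analysis, or that the protocol announces it will throw diaries away. It says neither. They remain in the randomised population with imputed values, and the setting aside of any observed outcomes follows only from a literal reading.

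Finally, a reader might infer that the rule favours EA. The documents do not support that. It needs an imputation model fitted within arm, which is not stated, and a suitable balance of non-starters, which is not given. Participants are blinded (2.4.6), so the protocol gives no reason to expect them to decline in one arm only. Acupuncturists are not listed as blinded, so balance is not assured either.

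**Conclusion.** The inconsistency is real but narrow. Section 8.3 makes treatment status the criterion for missing data in never-treated participants, and this conflicts with section 8.2 over the use of their observed outcomes, not over who is analysed.

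The likely effect on the primary result is small: at most 0.024 CSBMs/week for equal untreated shares up to 5%, under within-arm imputation and a common untreated mean. One-sided non-starting would give more, up to +0.075 (EA only) or −0.051 (SA only) at 5% with no change in the untreated. The shares and the untreated mean are assumptions, and the direction cannot be settled from the documents. The sentence is worth correcting because it governs the primary endpoint and the correction is nearly free, not because a material bias has been shown.

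**What to change.** Replace the sentence in section 8.3 with: *Outcome data are missing only where they were not obtained; all outcome data collected from randomised participants are used in the primary analysis, whether or not any treatment was received; missing data are multiply imputed.*

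This brings 8.3 into line with 8.2 and with the follow-up provisions in 2.4.7.3 and 6.3. It costs one changed sentence and needs no new data; the estimate may differ slightly, in a direction that cannot be predicted. The imputation model can stay in the SAP. A sensitivity analysis that imputes untreated participants from the SA arm is optional and not part of this correction.
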